### Sample Size and Statistical Analysis

At the time of the study planning, data from the Lleida health care region had identified 1388 people with T2DM treated with MDI. On the basis of prior clinical experience, approximately 25% of these individuals may have sufficient residual β cell function to discontinue prandial insulin. To estimate this proportion with a 95% CI and a margin of error of –5% to +5%, a sample size of 239 participants was estimated.

The study population will be characterized at baseline with respect to age, BMI, duration of diabetes, presence of chronic diabetes-related complications (microvascular and macrovascular), and cardiovascular risk factors. In addition, in-depth phenotyping will be performed using the homeostatic model assessment of β cell function and homeostatic model assessment of insulin resistance indexes [27] and GADAb measurements.

For the primary outcome, the proportion of participants who discontinue prandial insulin after the application of the diagnostic algorithm and sustain this change over a 6-month follow-up period will be calculated, along with its corresponding 95% CI.

Secondary outcomes will include measures of glycemic control, patient-reported outcomes, and safety outcomes. Glycemic control will be assessed using HbA_1c_ and CGM-derived metrics, including time in range (70‐180 mg/dL), time below range, time above range, mean glucose, and glycemic variability indexes. Patient-reported outcomes will include validated scores for treatment satisfaction, adherence, and quality of life analyzed according to each instrument’s scoring manual. Safety outcomes will include the incidence of severe hypoglycemia.

To evaluate changes over time (eg, from baseline to follow-up visits), paired 2-tailed *t* tests or Wilcoxon signed-rank tests will be used depending on data distribution. Between-group comparisons (eg, discontinuation vs continuation of prandial insulin) will be conducted using Student *t* tests or Mann-Whitney *U* tests as appropriate, as well as using linear mixed-effects models to account for within-subject correlation.

For categorical secondary outcomes, including severe hypoglycemia, comparisons between groups will be performed using chi-square or Fisher exact tests as appropriate. For outcomes measured repeatedly across follow-up visits, analyses will be conducted using linear mixed-effects models.

CGM variables will also be examined as potential predictors of pancreatic reserve and insulin resistance. Depending on whether outcomes are continuous or categorical, linear or logistic regression models will be applied. Results will be expressed as regression coefficients or odds ratios with corresponding 95% CIs.

Loss to follow-up will be quantified and reported as the proportion of participants without outcome data at each follow-up time point. When available, reasons for loss to follow-up will be documented. Baseline characteristics of participants with complete follow-up and those lost to follow-up will be compared to assess potential differential attrition. A complete-case analysis will be used as the primary analytical approach when the proportion of missing data is low, and missingness will be considered compatible with a missing completely at random mechanism. To account for potentially informative missingness, multiple imputation by chained equations will be performed under a missing-at-random assumption, including all variables used in the main analyses and auxiliary variables related to missingness.

All statistical analyses will be performed using the R software (version 4.1.2; R Foundation for Statistical Computing), with a 2-sided *P* value of <.05 considered statistically significant.

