### Recruitment and Sampling Strategy

The participant selection sampling strategy was a convenient approach based on the availability and willingness to participate of the patients who fulfilled the study criteria [21].

Participating centers were selected based on geographic distribution and availability of primary health care teams. Teams received virtual training sessions. Sessions included information related to the background, objectives, protocol procedures, and data collection methods before participant recruitment. The study recruitment period lasted 6 months.

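### The 239 participants give ±5 points at 25% only through an unnamed finite-population correction that fits poorly with a convenience sample and wider inference; ordinary precision is about ±5.5 points

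*Protocol article*

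**What the plan says.** All of the sizing stands in one paragraph of the protocol article, under Sample Size and Statistical Analysis. It first gives a population: "data from the Lleida health care region had identified 1388 people with T2DM treated with MDI". It then says that "approximately 25% of these individuals may have sufficient residual β cell function to discontinue prandial insulin", and sets the target: "To estimate this proportion with a 95% CI" and a "margin of error of –5% to +5%, a sample size of 239 participants was estimated". No formula or correction is named.

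For the primary outcome, the same section says that the proportion who stop prandial insulin and stay off it for 6 months "will be calculated, along with its corresponding 95% CI". The type of interval is not given.

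Under Recruitment and Sampling Strategy: "The participant selection sampling strategy was a convenient approach based on the availability and willingness to participate". Centers were chosen by geography and by whether teams were available. The Limitations section acknowledges convenience recruitment and possible selection bias. Expected Findings, in the Discussion, hopes for uptake by clinicians who treat type 2 diabetes in general.

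On missing data: "Loss to follow-up will be quantified and reported as the proportion of participants without outcome data", and "A complete-case analysis will be used as the primary analytical approach when the proportion of missing data is low", with multiple imputation where missingness may be informative. The sizing paragraph states no allowance for loss.

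**The concern.** A reader who checks the sample size with the standard formula for one proportion gets 289, not 239. The 50-participant gap is closed only by a finite-population correction, which the reader has to infer from the 1388 mentioned two sentences earlier.

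The correction is not a neutral detail. It shrinks the standard error because part of a fixed, known population has been observed by random sampling without replacement, and it answers a question about that population only. Participants here were recruited by availability and willingness, and the result is meant to inform practice more widely.

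The ±5 points is the only precision or power property that the article states. If the published interval is an ordinary binomial one, it will be wider than the plan announced, and readers may wonder why.

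**Working it through.** **Inputs** (all from Sample Size and Statistical Analysis): p = 0.25; 95% confidence, z = 1.96; half-width d = 0.05; N = 1388. The Discussion agrees with N: 5% of 27,769 is 1388.

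**Step 1. Reproduce the stated figure.**
- Standard formula: n0 = z² p(1−p)/d² = 1.96² × 0.25 × 0.75 / 0.05² = 288.1, rounded up to 289. This is not 239.
- With the correction: n = n0 / (1 + (n0 − 1)/N) = 288.1 / (1 + 287.1/1388) = 238.7, rounded up to 239. This matches.
- Other uncorrected choices do not match: a 90% CI gives 203, z = 2 gives 300, p = 0.5 gives 385, p = 0.20 gives 246.

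**Step 2. Half-width at 239 and p = 0.25.**
- Uncorrected: 1.96 × √(0.1875/239) = 0.0549, that is 5.49 points.
- Corrected: 0.0549 × √((1388 − 239)/(1388 − 1)) = 0.0549 × 0.910 = 0.04997, that is 4.997 points.

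**Step 3. Does the interval type matter?** For 60 of 239 (25.1%), without correction:

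| Interval | Limits | Half-width (points) |
|---|---|---|
| Wald | 19.6% to 30.6% | 5.50 |
| Wilson | 20.0% to 31.0% | 5.47 |
| Clopper-Pearson | 19.7% to 31.1% | 5.68 |

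(At exactly p = 0.25, Wald gives the 5.49 of step 2.) All are about 5.5 points or a little more. Read the other way, an uncorrected ±5-point interval at 239 has about 92.6% nominal confidence.

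**Step 4. Room for loss to follow-up, at p = 0.25.** The article gives no loss rate, so the rates below are assumptions.

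| Evaluable | Assumed loss | Corrected (points) | Uncorrected (points) |
|---|---|---|---|
| 239 | none | 4.997 | 5.49 |
| 238 | 1 person | 5.01 | 5.50 |
| 227 | 5% | 5.15 | 5.63 |
| 215 | 10% | 5.32 | 5.79 |
| 191 | 20% | 5.70 | 6.14 |

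The row for 238: 1.96 × √(0.1875/238) = 0.0550; times √(1150/1387) = 0.911 gives 0.0501. Even with the correction granted in full, one lost participant takes the half-width past 5 points.

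**The case against.** The strongest reply is that the article does what it says. It opens the sizing paragraph with the 1388 people, takes 25% of them, and sizes the study to estimate that proportion. For that target a finite-population correction is standard, its one extra input is printed, and 239 follows exactly. This stands. A reader might infer that the sample size is miscalculated, or that 239 flatly fails to give ±5; the documents do not support either when the target is those 1388 people and all 239 are evaluable.

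Second, convenience sampling weakens any design-based interval, including the uncorrected 5.5 points and the 289. This also stands: a larger sample would not cure selection, and the article discloses the limitation. But it does not rescue the correction, which depends on the same missing random draw and also confines the inference to the region.

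Third, the interval method may be fixed in a full protocol or analysis plan that is not shown. This is fair. The article does not say that the interval will be uncorrected, and its silence is not a defect. The 5.5 points is what an ordinary interval would give, not a prediction of what will be published.

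Fourth, complete-case analysis is conditional on low missingness, and the loss rates above are assumed. Also fair; the 20% row in particular may not count as low. The absence of slack at 239 does not depend on any of these rates.

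One further inference should be resisted. The 25% is described as having enough β cell function to stop, whereas the primary outcome is stopping and staying off. The two can differ, but this does not show a shortfall: if fewer people stay off than have the capacity, the proportion falls and the interval narrows. At about 19%, 239 gives ±5 points even uncorrected.

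**Conclusion.** The point holds as an unsupported precision assumption, not as an arithmetic error. The stated ±5 points at 25% rests on an unnamed correction whose conditions, random sampling from the 1388 and inference limited to them, do not match the recruitment described or the wider use envisaged. Without it, 239 evaluable participants give about ±5.5 points, and ±5 would need 289. The difference is about half a point of half-width. It grows to about 0.8 point with an assumed 10% loss (5.8 uncorrected; 5.3 even with the correction).

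These figures assume p = 0.25. The uncorrected ones treat the sample as if it were random, so they describe nominal precision only and take no account of selection. No test, decision threshold or stopping rule in the article hangs on ±5. Severity is minor to moderate.

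**What to change.** Replace the precision statement with wording such as:

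> With 239 evaluable participants and an expected proportion of 25%, the ordinary 95% CI half-width is about 5.5 percentage points (about 5.8 if 10% are missing); the ±5 figure applies only with a finite-population correction for the 1388 people in the region.

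Then fix the primary interval to match its target: report it without the correction if the result is to be generalised beyond those 1388 people. If the result is meant for them alone, name the correction and use it in the interval as well.

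The cost is one sentence and a slightly less favourable stated figure. Recruitment has ended, and no extra enrolment is needed. By the article's account, analysis begins only after follow-up, so the statement can be settled before results are known.

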### Eligibility Criteria

We included adults aged ≥18 years with a confirmed diagnosis of T2DM. To be enrolled in the study, participants must be on an MDI regimen, defined as receiving at least 2 doses of prandial insulin per day (either regular insulin or a rapid-acting insulin analogue) administered separately or as part of a fixed-dose combination.

We excluded individuals with a known diagnosis of diabetes other than T2DM, pregnant women, and those with severe cognitive impairment or any condition that prevented the use of CGM. We also excluded participants with current drug or alcohol abuse, those receiving systemic glucocorticoids for acute conditions at the time of inclusion, and individuals undergoing temporary insulin therapy expected to last less than 6 months.

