### Study Procedures and Timeline

Potential participants were identified by local study physicians and nurses using the primary care eCAP (Catalan Health Institute) electronic clinical record software. Each participant underwent 4 study visits. Initially, a preselection visit was conducted through electronic health record review without direct patient contact. Eligible individuals were then contacted and provided with detailed study information. Those who agreed to participate were invited to the inclusion visit (visit 0), during which written informed consent was obtained by research staff. This visit involved a clinical interview, a physical examination, laboratory testing (including C-peptide and GADAb measurements), and the placement of a CGM device. All participants used CGM for 10 to 15 days prior to the intervention. Two weeks later, the first follow-up visit (visit 1) was conducted. At this visit, therapeutic decisions were made based on C-peptide and GADAb results, and treatment was adjusted according to the predefined therapeutic intervention algorithm (Figure 1).

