### Data Collection and Management

#### Overview

Data for this study are collected from electronic medical records and patient-reported questionnaires during study visits. Clinical and demographic information, including age, sex, educational level, BMI, diabetes duration, comorbidities, complications, and current pharmacological treatment, is obtained from the eCAP (electronic medical record) software and supplemented by medical interviews. Laboratory variables, including C-peptide, GADAb, HbA_1c_, and estimated glomerular filtration rate, are extracted from recent laboratory reports or requested when unavailable. CGM data, including metrics such as time in range, hypoglycemia episodes, and glucose variability, are downloaded directly from the devices used by participants throughout the study. Patient-reported outcomes, including quality of life, treatment satisfaction, medication adherence, and physical activity, are assessed using validated questionnaires. All study variables and corresponding time points are summarized in Table 1. In addition, detailed information on the study variables, including their definitions and data sources, is provided in Multimedia Appendix 2.

**Table 1. T1:** Study timeline, variables, and procedures.

Data collected	Evaluation time point			
	Preselection	Visit 0—inclusion	Visit 1—intervention (2 weeks)	Visit 2—final follow-up (6 months)
Inclusion and exclusion criteria	✓	✓		
Sociodemographic data^a^		✓		
Anthropometric data^b^		✓		✓
Clinical data^c^		✓		✓
CGM^d^ data			✓	✓
Laboratory data^e^		✓		✓
Smoking status		✓		
Pharmacological treatment^f^		✓		✓
Severe hypoglycemia^g^		✓		✓
Questionnaires^h^		✓		✓

a Age, gender, primary care center, current occupational status, level of education, number of children, date of menopause, and whether the participant is the sole caregiver of another person.

b Weight, height, BMI, and abdominal circumference.

c Arterial hypertension, dyslipidemia, micro- and macrovascular complications, heart failure, and renal disease of any etiology (estimated glomerular filtration rate <60 mL per minute per 1.73 m2).

d CGM: continuous glucose monitoring.

e Inclusion visit: hemoglobin A_1c_ (HbA_1c_), glutamic acid decarboxylase autoantibody, glycemia, and C-peptide; final visit: HbA_1c_.

f Prescription and dosage of diabetes drugs.

g Inclusion visit: last 12 months; final visit: 6 months of study.

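### HOMA-IR, the only insulin-resistance index named, omits injected insulin if formed from C-peptide, and every participant is injecting insulin at baseline

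*Protocol article*

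**What the plan says.** Four statements in the protocol article bear on this.

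- Sample Size and Statistical Analysis, on baseline characterization: "in-depth phenotyping will be performed using the homeostatic model assessment of β cell function and homeostatic model assessment of insulin resistance indexes". No formula, HOMA version or input is given. The same section later adds: "CGM variables will also be examined as potential predictors of pancreatic reserve and insulin resistance". Study Outcomes lists that same association. HOMA-IR is the only insulin-resistance index named.
- Eligibility Criteria: "participants must be on an MDI regimen, defined as receiving at least 2 doses of prandial insulin per day". Injected insulin is therefore universal at entry.
- Study Procedures and Timeline: the inclusion visit includes "laboratory testing (including C-peptide and GADAb measurements), and the placement of a CGM device". Only at visit 1, two weeks later, do we read that "treatment was adjusted according to the predefined therapeutic intervention algorithm". No insulin-free interval before sampling is described.
- Data Collection and Management, Table 1 footnote e: "Inclusion visit: hemoglobin A_1c_ (HbA_1c_), glutamic acid decarboxylase autoantibody, glycemia, and C-peptide; final visit: HbA_1c". The accompanying text says: "Laboratory variables, including C-peptide, GADAb, HbA_1c_, and estimated glomerular filtration rate, are extracted from recent laboratory reports or requested when unavailable". Neither names an insulin assay. The final visit has HbA1c only, so the indexes cannot be recomputed after prandial insulin has been stopped.

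**The concern.** HOMA-IR reads insulin resistance from the steady-state product of glucose and the insulin acting on it. In someone who injects insulin, part of that insulin does not come from the pancreas, and C-peptide does not register that part. An index built from glycemia and C-peptide therefore credits injected insulin's effect on glucose to better insulin sensitivity. More resistant people tend to need more injected insulin, so the error is likely to be largest where resistance is highest.

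Two analyses are at stake: the insulin-resistance part of the baseline phenotyping, and the regressions with insulin resistance as the outcome and CGM metrics as predictors. If the outcome largely reflects secretion and injected dose, a regression coefficient or odds ratio for insulin resistance cannot be read as one.

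**Working it through.** **The plan's own figure.** The article gives no HOMA figure to reproduce. The one calculation in the same section is the sample size: n0 = 1.96² × 0.25 × 0.75 / 0.05² = 288.1. With the finite-population correction for 1388 people, 288.1 / (1 + 287.1/1388) = 238.7, which rounds up to the stated 239. HOMA plays no part in it.

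**Assumed relations.** I take the simple HOMA forms, with C-peptide expressed as equivalent endogenous insulin. G is fasting glucose (mmol/L), S is endogenous insulin and E the injected contribution (both mU/L), R is true resistance and B is beta-cell function (%).

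- Resistance: G × (S + E) = 22.5 × R
- Secretion: S = B × (G − 3.5) / 20
- HOMA-IR from C-peptide: G × S / 22.5 = R − G × E / 22.5
- HOMA-B from C-peptide: 20 × S / (G − 3.5)

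The third line is the finding. The index is too low by G × E / 22.5.

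**Two illustrative participants, B = 40 in both** (values assumed).

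- R = 3, E = 3: 2G² − 4G − 67.5 = 0, so G = 6.89 and S = 6.79. HOMA-IR from C-peptide = 2.08.
- R = 6, E = 15: 2G² + 8G − 135 = 0, so G = 6.46 and S = 5.91. HOMA-IR from C-peptide = 1.70.
- With E = 0, the same two people give G = 7.82 and 10.15, and HOMA-IR = 3.0 and 6.0, the right order.

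The more resistant person ranks lower. Reversal is not automatic: with E = 12 in place of 15 the second person scores 2.23, just above 2.08, so the order survives but a true difference of 3 shrinks to 0.15.

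**Growth with injected insulin, R = 6 and B = 40.**

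| E | HOMA-IR from C-peptide | Shortfall from 6 | HOMA-B from C-peptide | HOMA-B from total insulin |
|---|---|---|---|---|
| 0 | 6.0 | 0 | 40.0 | 40.0 |
| 12 | 2.23 | 3.77 | 40.0 | 107.4 |
| 15 | 1.70 | 4.30 | 40.0 | 141.5 |
| 18 | 1.27 | 4.73 | 40.0 | 189.1 |

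**How often order is lost.** I used 12 scenarios of 20,000 draws. R and B were independent and log-normal around 5 and 30, with log-SD 0.3 or 0.5. Glucose was centred on 8 or 9 mmol/L with SD 0, 1.5 or 2.5. E was solved from the equations, and only draws with E > 0 were kept.

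- Rank correlation of C-peptide HOMA-IR with true resistance: 0.08 to 0.33.
- Rank correlation with injected insulin: −0.17 to −0.77.
- Pairs ordered wrongly: 38% to 47%, where 50% would be no information.
- With everyone at the same glucose (SD 0), the index ranks people exactly by B (rank correlation 1.0).

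**The case against.** **An insulin assay may exist.** The footnote is not exhaustive: the text counts estimated glomerular filtration rate among the laboratory variables, and footnote e omits it. Definitions and sources are in Multimedia Appendix 2, which is not shown. So the absence of an assay is a reading of what is listed, not a certainty. An assay would not settle the matter, however. In the same equations a total-insulin measurement returns the right R, but HOMA-B then counts injected insulin (last column of the table). No single input serves both indexes.

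**HOMA version and fasting conditions are details an article may leave out.** This is accepted, and their absence is not the complaint. The complaint is a stated index applied to a stated population with a stated panel.

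**Stronger readings to avoid.**

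- A reader might infer that C-peptide HOMA-B also rises with injected dose. If secretion is held fixed while glucose falls from 10 to 6 mmol/L, the index multiplies by 6.5/2.5 = 2.6. But in the HOMA relation secretion falls with glucose: at B = 40, S drops from 13 to 5 and HOMA-B is 40 both times.
- A reader might infer that low C-peptide with a high dose proves misranking. It does not, because a person may inject more through secreting less.
- A reader might infer that the phenotyping could mislead about who can do without prandial insulin. The Intervention Algorithm section uses C-peptide and GADAb only, and HOMA enters no treatment decision.
- A reader might infer that the lowest C-peptide group will be reported as the most insulin sensitive. No tabulation of HOMA-IR by C-peptide group is planned.

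**Conclusion.** The point holds for HOMA-IR. Formed from the listed glycemia and C-peptide, it is biased downward in a cohort that all injects insulin, by an amount that grows with injected insulin, and it can put participants in the wrong order. The direction follows from the HOMA relations themselves. The size (2.08 against 1.70 for true values of 3 and 6; 38% to 47% of pairs misordered) rests on assumed values and distributions, including independence of resistance and beta-cell function, and is not an estimate for this cohort.

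The reach is limited to the insulin-resistance part of the phenotyping and the CGM regressions on insulin resistance. The secondary objective on phenotyping names pancreatic function and autoimmunity, for which C-peptide and GADAb are measured directly. The primary outcome, the treatment algorithm and N = 239 do not depend on HOMA.

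**What to change.** - Do not use HOMA-IR as the measure of insulin resistance in the baseline phenotyping, or as the outcome in the CGM regressions. At most report it as exploratory, from fasting glucose and C-peptide in the same draw, with no conclusion on insulin resistance. The same-draw condition needs stating because laboratory values may come from existing reports.
- Describe insulin resistance by BMI, abdominal circumference and total daily insulin dose per kg. Read the dose alongside C-peptide, because it also reflects insulin deficiency and is not a clean marker of resistance by itself.
- Report pancreatic reserve primarily by C-peptide with its paired glycemia. C-peptide-based HOMA-B may stay as a supplement.
- If an insulin assay does exist, state which input feeds which index.

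The cost is analysis wording only. Weight, BMI, waist, diabetes-drug dosage, glycemia and C-peptide are all in Table 1, and the Results section says formal analysis had not started when the article was written. The one loss is comparability with cohorts that report HOMA-IR.

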## Abstract

**Background:**

The management of type 2 diabetes mellitus (T2DM) remains a complex clinical challenge, particularly for patients requiring multiple daily insulin injections (MDI). Advances in precision medicine and continuous glucose monitoring (CGM) have created opportunities to personalize treatment and potentially reduce the therapeutic burden on people with T2DM. Assessing β cell function and autoimmunity could help identify patients with T2DM eligible for simplified regimens without compromising glycemic control.

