### Hypothesis and Objectives

We hypothesize that approximately 25% of people with T2DM on MDI have sufficient β cell secretory capacity to safely discontinue prandial insulin. In these cases, treatment could be optimized by introducing agents with proven cardio-renal or weight-lowering benefits according to current clinical guidelines.

The main objective is to evaluate a simple personalized medicine protocol in routine clinical practice for people with T2DM on MDI. The protocol, based on clinical and analytical parameters, aims to improve diagnostic accuracy and potentially simplify treatment in this population.

Secondary objectives include describing patient characteristics; conducting detailed phenotyping of pancreatic function and autoimmunity status; and evaluating the impact of the intervention on glycemic control, treatment adherence, and quality of life.

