## Discussion

### Expected Findings

According to data from the Catalan Agency for Health Quality and Assessment and the eCAP electronic medical record system, the Lleida health care region has approximately 27,769 individuals diagnosed with T2DM, representing 8.95% of the adult population. Among these patients, 5% are currently treated with MDI.

This study aims to improve the available evidence in precision medicine for T2DM, specifically targeting patients treated with MDI. Using the simple precision medicine algorithm (Figure 1) proposed in this study based on assessment of β cell function (C-peptide) and autoimmunity (GADAb), we will evaluate whether prandial insulin can be safely removed or replaced by another treatment in real-world clinical practice.

The study’s main outcome is the proportion of patients in whom prandial insulin is successfully discontinued and remains unnecessary at 6 months. Secondary outcomes include clinical measures such as HbA_1c_ levels; CGM-derived metrics related to insulin resistance and pancreatic function; incidence of severe hypoglycemia; and several patient-reported outcomes—including quality of life, treatment satisfaction, medication adherence, and physical activity. Among patients who continue prandial insulin and CGM, the study also examines the added value of CGM use on both metabolic control and patient experience.

The algorithm is implemented by a multidisciplinary research team—including general practitioners, endocrinologists, and nurses—who integrate biomarker results with patient-specific clinical characteristics to guide medical decision-making. The strategy proposed by this study is intended for inclusion in clinical practice. If successful, this approach could be adopted by health care professionals managing T2DM to achieve simpler, safer, and more effective treatment strategies, particularly those that offer cardiovascular, renal, and weight management benefits.

This personalized strategy aligns with a broader innovation trend in diabetes care. Similar to the study by Dennis et al [28], which developed and validated a predictive model to individualize glucose-lowering therapies in T2DM, our project aims to move beyond conventional treatment algorithms by incorporating patient-specific pathophysiological characteristics.

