### Conclusions

More accurate phenotyping of persons with T2DM on MDI may improve diagnostic accuracy and enable treatment optimization by identifying candidates for prandial insulin withdrawal or for the introduction of agents with better safety profiles and added cardiovascular benefits [30].

Simplifying therapeutic strategies in T2DM management can be effective provided that personalized care is prioritized, patient safety is preserved, and glycemic control is maintained.

Furthermore, implementing CGM represents both a challenge and an opportunity to enhance diabetes care across primary care and endocrinology services. Strengthening collaboration across care levels and promoting the use of digital health tools may empower patients and improve the management of this highly prevalent and impactful chronic disease.

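### HbA1c change in people who stop prandial insulin is assessed only by two-sided difference tests, which cannot support a statement that control was not worsened

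*Protocol article*

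**What the plan says.** The hypothesis (Hypothesis and Objectives) is that roughly a quarter of people with T2DM on multiple daily injections "have sufficient β cell secretory capacity to safely discontinue prandial insulin". Expected Findings puts the study question as: "we will evaluate whether prandial insulin can be safely removed or replaced by another treatment in real-world clinical practice".

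Under Study Outcomes, the primary outcome is the proportion taken off prandial insulin and still off it at 6 months. No glycemic condition is attached. HbA1c and CGM metrics are secondary. The Intervention Algorithm section adds that CGM is usually withdrawn from those who stop prandial insulin, because public funding no longer applies.

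For glycemic change, Sample Size and Statistical Analysis states: "To evaluate changes over time (eg, from baseline to follow-up visits), paired 2-tailed" t tests, or Wilcoxon signed-rank tests. It continues: "Between-group comparisons (eg, discontinuation vs continuation of prandial insulin) will be conducted using Student" t or Mann-Whitney tests, together with linear mixed-effects models. The significance rule is two-sided P<.05 throughout. A 95% CI is promised for the primary proportion and for the coefficients and odds ratios of the CGM-predictor models, but not for the HbA1c change. The sample size of 239 is derived from the precision of a proportion.

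**The concern.** Whether a treatment can be withdrawn without harm to control is a question of the form: is it not worse? A difference test answers another question. When it rejects, it shows a change. When it does not reject, it shows only that the data could not separate the change from zero, and this happens more readily the smaller and noisier the group is.

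The primary outcome cannot fill the gap, since a participant who is off prandial insulin at 6 months counts as a success whatever the HbA1c. With CGM usually stopped in the same people, HbA1c carries most of the glycemic evidence in the group of interest. Comparison with those who continue insulin does not repair this: it is again a difference test, and the algorithm separates the two groups by C-peptide and GADAb.

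At stake is the sentence clinicians would act on, namely that people selected by this algorithm kept their glycemic control after stopping prandial insulin. The inference as stated gives that sentence no positive support.

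**Working it through.** **Inputs from the article:** source population 1388; expected proportion 25%; margin of error ±5 points; 95% confidence; N = 239; two-sided alpha .05.

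**Assumed, because the article does not give it:** SD of the within-person HbA1c change, 0.8 to 1.5 percentage points. The rises of 0.3, 0.4 and 0.5 points below are illustrations, not proposed margins.

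**1. The plan's own figure.** n0 = z²p(1−p)/d² = 1.96² × 0.25 × 0.75 / 0.05² = 288.1. With the finite population correction, n = 288.1 / (1 + 287.1/1388) = 238.7, so 239. The stated number reproduces exactly. It concerns the proportion only.

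**2. Expected number stopping.** 0.25 × 239 = 59.75, about 60.

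**3. Precision of the HbA1c change.** Half-width = t(0.975; 59) × SD/√60, with t = 2.00.

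**4. Chance that a real rise gives P≥.05.** Paired t test, noncentral t with 59 df and noncentrality δ√60/SD. Example: δ = 0.3 and SD = 1.0 give 0.3 × 7.75 / 1.0 = 2.32 against a critical value of 2.00, so the miss probability is 37%.

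| n = 60 | SD 0.8 | SD 1.0 | SD 1.2 | SD 1.5 |
|---|---|---|---|---|
| 95% CI half-width (points) | 0.21 | 0.26 | 0.31 | 0.39 |
| True rise 0.3 missed | 18% | 37% | 52% | 67% |
| True rise 0.4 missed | 3% | 14% | 28% | 47% |
| True rise 0.5 missed | <1% | 3% | 11% | 28% |
| Upper limit when P is just above .05 | 0.41 | 0.52 | 0.62 | 0.77 |

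The last row is twice the half-width: an observed rise just short of significance is compatible with a true rise of that size.

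**5. Loss to follow-up (assumed 10% to 20%).** With 54 to 48 people, a 0.3-point rise at SD 1.0 is missed in 42% to 47%.

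**6. Between-group test, 60 against 239 − 60 = 179.** A difference of 0.3 SD is missed in 48%, 0.4 SD in 24% and 0.5 SD in 8%.

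**7. Could a CI-based rule succeed?** With no true change and 60 people, the chance that the upper 95% limit falls below an illustrative limit is as follows for SD 0.8/1.0/1.2/1.5: 82/63/48/33% for 0.3 points, 97/86/72/53% for 0.4, and >99/97/89/72% for 0.5. The rule can be met, but not with certainty.

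**The case against.** A reader might infer that the investigators intend to read a non-significant HbA1c test as proof of maintained control. The article does not say so anywhere, and no such decision rule can be attributed to it.

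The wording closest to a maintained-control claim is also weaker than it looks. The Abstract's Background says that biomarker assessment "could help identify patients with T2DM eligible for simplified regimens without compromising glycemic control", which is hedged rationale. The closing Conclusions say: "Simplifying therapeutic strategies in T2DM management can be effective provided that personalized care is prioritized, patient safety is preserved, and glycemic control is maintained". That is a condition for practice, not a result the study undertakes to declare. The stated secondary objective is neutral in direction (the impact on glycemic control), and a two-sided comparison fits it. The safety outcome is severe hypoglycemia, so safe removal need not mean unchanged HbA1c. HbA1c is secondary in a study that calls itself feasibility-focused, and not sizing for a secondary outcome in a subgroup is normal. A full protocol or analysis plan, not shown, may hold more detail.

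All of this stands and narrows the point. It does not remove it. The article does state its HbA1c tests and significance rule, so the issue is a mismatch between what is stated and the question asked, not a missing detail. Its Conclusions also set maintained glycemic control beside patient safety as a condition for success, so a statement on glycemia will be wanted.

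The figures are conditional as well. The SD is assumed, the 25% rests on the team's clinical experience, and the number enrolled is not given. If 25% describes those still off insulin at 6 months, the group stopped at Visit 1 would be at least as large and precision better.

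Finally, there is no control group. New agents, closer follow-up and regression to the mean all enter the before-after change, so meeting a limit would not show that stopping insulin itself preserved control.

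**Conclusion.** The point holds in limited form. The HbA1c inference stated in the article can detect worsening but cannot support a statement that control was not worsened, and the sample size gives no assurance on this. With about 60 people stopping, a non-significant paired test could hide a mean rise of 0.3 points in 18% to 67% of studies, or 0.4 points in 3% to 47%, for an assumed SD of change of 0.8 to 1.5 points. At SD 1.0 or below, a 0.5-point rise would be missed in at most about 3%, so large average deterioration is fairly well covered. The weakness lies in modest worsening.

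This does not touch the primary proportion or its confidence interval. Nor does it show that the investigators plan a wrong conclusion: the stated analysis simply gives them no sound basis for the favourable one.

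**What to change.** Before the data are analysed, add a few sentences to the analysis section:

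- In all participants whose prandial insulin was stopped at Visit 1, including any who later resumed it, report the mean HbA1c change to 6 months with its two-sided 95% CI. State the expected half-width, about 0.2 to 0.4 points for 60 people under the SDs assumed above.
- Base any statement that control was maintained on the upper limit of that interval, compared with a tolerable rise that the clinical investigators fix and date before analysis.
- State that P≥.05 will not be read as maintained control, and that the result is inconclusive if the upper limit is not below the tolerable rise.
- Describe the finding as a before-after change without a control group, not as causal non-inferiority.

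The change uses HbA1c values already scheduled at inclusion and at Visit 2. By the Results section, formal analysis starts only after follow-up closes. The tolerable rise would be set late, after recruitment ended, so the report should say when it was fixed. The main cost is a stricter claim that may end inconclusive: with no true change, a 0.4-point limit (illustration only) would be met in 97% of studies at SD 0.8 but 53% at SD 1.5. If no limit can be agreed, reporting the interval and disclaiming non-significance as evidence of maintained control is the minimum.
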